### Blinding

Occupational therapists and physiotherapists in the municipality will conduct the baseline assessments in the participant’s home prior to randomisation. The research assistants, who are also occupational therapists and physiotherapists, will be blinded to group allocation and perform all follow-up assessments. The research assistants will urge the participants not to reveal their group allocation during follow-up assessments, which will also take place in the participant`s home. The success of research assistant blinding will be evaluated for both follow-ups. Due to the nature of the interventions, it will not be possible to blind participants and health-care providers. Researchers performing data entry and data analysis will, however, be blinded to group allocation.

### Training of the intervention providers

Reablement will be implemented in the municipality after a period of administrative planning and competence-building. The competence-building will involve all the members of the multidisciplinary reablement team, such as nurses, auxiliary nurses, social educators, occupational therapists, physiotherapists, home-helpers and assistants. The health-care providers will be given lectures and seminars, and invited to attend external courses. Special attention will be given to the use of the Canadian Occupational Performance Measure (COPM)
[12], a patient-specific measure which will be used to identify activity limitations and as a basis for formulating the goals that will be addressed in the reablement intervention. It will also be important to ensure that all members of the reablement team have internalised the required rehabilitation approach of encouraging the participant to self-management.

### Interventions

#### Reablement

The intervention will have a maximum duration of 3 months. As part of baseline assessments, the occupational therapist and physiotherapist will use the COPM interview to identify activity limitations perceived as important by the participant. This information will thereafter be used to develop a rehabilitation plan, and to ensure congruence between the participant’s needs, therapy priorities, and interventions. After initiating the reablement intervention, the occupational therapist and physiotherapist will supervise the home-care personnel, some of whom have no formal education, in how to encourage and assist the person in the daily training. The focus is on stimulating the participants to do the daily tasks themselves, rather than receiving help or letting others do the tasks for them. As reablement is tailored according to participants’ goals, the components of the invention will vary. However, the intervention will consist of both general and individual features as described in Table 
1.

**Table 1 Tab1:** **Features of the reablement intervention**

General features	Individual features
• The rehabilitation period will be a maximum of 3 months.	• *Training in daily activities* such as dressing, food preparation, vacuuming, bus transport, visiting friends at a club, or being able to knit.
• An occupational therapist or physiotherapist will conduct the COPM interview and develop the rehabilitation plan together with the participant based on the identified activity goals. Thereafter, an integrated multidisciplinary team with shared goals will guide the participant during the whole rehabilitation period.	• *Adaptations* such as advice on appropriate assistive technology or adapting the activity itself or the environment, in order to simplify activity performance.
• In addition to home-care personnel assisted training, a minimum of one hour physiotherapist and/or occupational therapist assisted training will be guaranteed each week.	• *Exercise programs* such as indoor or outdoor walking with or without walking aids, climbing stairs, transferring, and performing exercises to improve strength, balance or fine motor skills. The exercises will be incorporated into daily routines and the person will be given a manual explaining each of the exercises and encouraged to train on their own.
• The treatment will involve repetitive training and multiple home-visits by health-care personnel, who will be present during daily training for the purposes of building confidence and relearning skills.	
• All health-care personnel will stimulate the participant in self-management and self-training.	

#### The control intervention

Standard treatment/care is the conventional treatment homebound persons in most municipalities in Norway are offered, and this will be used as the comparator. For most participants, standard treatment will involve receiving the compensating help they apply for, in terms of personal or practical assistance, Meals on Wheels, safety alarm or assistive technology. However, for some participants, it may comprise rehabilitation by an occupational therapist and/or physiotherapist based on the participants’ own efforts. Hence, the standard treatment will also be diverse. The standard treatment will not be time-limited, and may continue after 3 months if needed.

### Outcomes

Data collection will involve the use of four different outcomes measures. In addition, cost outcomes in terms of consumption of different home-based services will be registered on a daily basis during the first 9 months after inclusion. This comprises registering minutes spent by different health professionals in the participant’s home. The first author will train all research assistants in how to conduct the data collection in order to obtain protocol adherence. Table 
2 provides an overview of the various outcomes that will be measured.

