## Background

The increasing aged population, in conjunction with an expected shortage of health-care personnel in developed countries, present a huge challenge to the containment of future health-care costs
[1]. Further, in times of budget cuts to front-line public services, policy makers are seeking new approaches to get more for less by investing the resources available in ways which have an optimal impact on outcomes
[2]. As a result, in recent years, there has been an increasing interest in home-care reablement services (hereafter ‘reablement’)
[3]. Reablement, termed ‘restorative care’ in US, Australia and New Zealand, is an approach to improve home-care services for older people needing care or experiencing functional decline. It is a goal-directed and intensive intervention, which takes place in the person’s home and local surroundings with a focus on enhancing performance of everyday activities defined as important by the person. The intention is to increase independence in daily activities, and enable people to age in place, be active and participate socially and societally. The health-care providers are organised in an integrated, coordinated multidisciplinary team that works together with the person towards shared goals
[4]. In Norway, a substantial proportion of municipalities are currently implementing reablement.

The effects of reablement have so far been evaluated in three randomised controlled trials (RCTs). Two of these were conducted in New Zealand, and the results showed improved social support and physical functioning
[5] and improved quality of life
[6]. In a third Australian RCT with 750 participants and a 2-year follow-up, reablement was compared with usual care
[7]. Even if the results showed few differences between groups in individual outcomes over time, a significantly smaller proportion of the reablement group required assistance with personal care. In a later publication from the same trial, the results showed that participants in the reablement group required fewer home-care hours, were less likely to be approved for a higher level of aged care such as nursing homes, and were less likely to be in need of emergency department treatment than the conventional care group
[8]. The results thereby indicate that reablement may reduce the need for ongoing home-care, as well as for other health care services.

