**Health-care services and cost measures**		
Warranted community-based assistance in time of inclusion	*Type of assistance wanted*	t1
	Home-helper/Nurse/Auxiliary nurse/Occupational therapist/Physiotherapist/Nursing home placement long term/Nursing home placement short term/Assisted living/Meals on Wheels/Safety alarm/Rehabilitation	
Inpatient and outpatient treatment since last assessment	*Frequency and type of co-interventions*	t2, t3
	Hospital admissions/Admissions to other institutions/Day centre placement/Outpatient treatment	
Current home-based assistance offered	*Presence and frequency of home-based assistance*	t2, t3, t4
	Home-helper/Nurse/Auxiliary nurse/Occupational therapist/Physiotherapist/Meals on Wheels/Reablement/No assistance	
Current community institution-based service offered	*Type of institution-based service offered*	t4
	Nursing home placement long-term/Nursing home placement short-term/Day placement/Other institution placement/No institution placement	
Usage of home-based services	*Daily time registration in minutes of working time used during home-visits*	t5
	Home-helper/Nurse/Auxiliary nurse/Occupational therapist/Physiotherapist/Social educator/Assistant/Speech therapist/Student	

t1 = baseline assessment, t2 = 3 months after baseline assessment, t3 = 9 months after baseline assessment, t4 = 15 months after baseline assessment, t5 = daily assessment during 9 months after baseline assessment.

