#### Health economic analysis

To assess potential welfare effects of the intervention, a cost-efficiency analysis (CEA) and a cost-utility analysis (CUA) will be conducted. Effect measures of the intervention are changes in COPM for the CUA and changes in e.g. grip strength for the CEA. Detailed registration of time spent at each home will enable us to establish the aggregate costs associated with provision of services for individuals in both groups. The hourly wage including pay roll tax and other taxes for the different categories of staff members will be applied. Costs will vary according to the duration and/or type of competence that is offered to each participant. The detailed time registration will make it possible to differentiate between types of staff with respect to costs. An incremental cost efficiency ratio (ICER) will be calculated.

Potential long-term changes in the intervention group will be examined after 15 months. Employing the panel data structure, variations in cost per unit change in effect measures across individuals will be analysed, controlling for gender, age, and other variables. Both fixed effect and random effect models will be estimated.

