One limitation in the study will be the lack of blinding of participants and health-care providers. We will, however, record and evaluate the success rate of the assessor blinding strategy. Another possible limitation will be the risk of contamination from the intervention arm of the study to the control arm. Due to potential problems with recruitment in a rather sparsely inhabited municipality, the intervention will be implemented in all home-care districts in the municipality. Hence, it will not be possible to avoid the same health-care personnel providing both the experimental and control interventions, even though this will be to different participants. As a consequence, the differences between the groups may be diminished.

A third limitation may be the nature of the COPM interview, which, in a previous study, was found to have a therapeutic effect independent of further interventions
[31]. In the COPM interview and scoring process, the participants in both groups will be encouraged to verbalise important activity limitations and participation restrictions. This may have an effect that results in perceptual and behavioural changes initiated by the participant, which again may blur the effects of the reablement intervention. On the other hand, reablement is a goal-directed and individualised intervention. The use of COPM will allow each participant to choose and rate the activity limitations that he/she considers important, thereby capturing aspects of everyday life that are of direct concern to the individual. As a consequence, the “noise” related to items in standardised instruments experienced as irrelevant by participants will be reduced, which in theory will have the potential to make the COPM more responsive to capturing the effects of reablement. In addition, the described activities will be used as a basis for discussing both long-term and short-term goals for reablement, thus enhancing communication and an active role for the participant in the reablement process.

In conclusion, this study will contribute to the knowledge of the effect and cost-effectiveness of reablement in community-dwelling adults.

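### Costs are built on staff minutes logged in the home, while reablement as described also uses staff time outside it, so reablement's cost would tend to be understated

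*Protocol article*

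**What the plan says.** The Outcomes section introduces the log as a cost measure: "cost outcomes in terms of consumption of different home-based services will be registered on a daily basis" for the first 9 months. It then specifies the content: "This comprises registering minutes spent by different health professionals", with the sentence going on to locate those minutes in the participant's home. The usage row of Table 2 (time point t5) gives the definition as "Daily time registration in minutes of working time used during home-visits", split by type of staff. The Health economic analysis section relies on it directly: "Detailed registration of time spent at each home will enable us to establish the aggregate costs" of services in both groups. Hourly wages are applied to that time and an incremental ratio is calculated.

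The intervention is described more widely. The Background places reablement in the person's "home and local surroundings with a focus on enhancing performance of everyday activities". Table 1 gives "bus transport, visiting friends at a club" among its examples of activity training, and outdoor walking among its exercise examples. The Reablement section adds that "the occupational therapist and physiotherapist will supervise the home-care personnel" once the intervention has started. Table 1 also guarantees at least one hour of therapist-assisted training a week, within a period of at most 3 months.

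**The concern.** The measure of resource use is narrower than the intervention it is meant to cost. Staff time spent on a bus, at a club or on an outdoor walk, and therapist time spent supervising home-care staff, belongs to delivering reablement but need not appear as minutes in the home.

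The gap is unlikely to be balanced. The section on the control intervention describes standard care for most participants as compensating help such as personal or practical assistance, delivered meals, a safety alarm or assistive technology. Therapist supervision of home-care staff is described only for reablement. Whatever the log leaves out would therefore be left out mainly in one arm.

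Cost-effectiveness is the second of the two research questions. Omitting input time in the experimental arm lowers its apparent cost, so the error would favour reablement.

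**Working it through.** The plan gives no figure for the amount or place of reablement staff time, so there is no stated number to reproduce. The check sets the definitions against the description and then follows the omission through the ratio.

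**1. What is counted.** Three places define or use the log: minutes in the home (Outcomes), working time during home visits (Table 2), and time at each home (Health economic analysis). None mentions time outside the home or supervision.

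**2. What reablement uses.** Home training, which is logged; training in local surroundings (Background, Table 1), logged only if treated as part of a home visit; and supervision of home-care staff (Reablement section), logged only if it takes place during a visit.

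**3. What control care uses.** Mostly compensating help. Some participants may receive rehabilitation from an occupational therapist or physiotherapist, so unlogged time in this arm need not be zero.

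**4. Effect on the ratio.** Let C be true mean staff cost per participant, U the mean cost of unlogged time and E the mean effect, with R for reablement and S for standard care.

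- True incremental cost = C_R − C_S.
- Computed incremental cost = (C_R − U_R) − (C_S − U_S) = (C_R − C_S) − (U_R − U_S).
- The incremental cost is therefore understated by U_R − U_S whenever U_R exceeds U_S. If reablement is the more effective arm, the ratio is understated by (U_R − U_S)/(E_R − E_S).

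**5. Illustration, on assumptions.** Take the guaranteed therapist hour over the maximum period: 1 h per week × about 13 weeks = 13 h. Assume a share s of it goes unlogged, with nothing unlogged in the control arm. Hours missed = 13 × s. With the 2-point COPM difference used in the sample size section as the effect, the ratio shifts by 13 × s / 2 therapist hours per COPM point.

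| Assumed share s | Hours missed per reablement participant | Shift, therapist hours per COPM point |
|---|---|---|
| 0% | 0 | 0 |
| 10% | 1.3 | 0.65 |
| 25% | 3.25 | 1.625 |
| 50% | 6.5 | 3.25 |

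The document supports no particular row. The table leaves out supervision and out-of-home time by home-care staff, for which it gives no amounts. It also assumes the full 3 months, which the protocol states as a maximum.

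**6. What is not affected.** The linear mixed models for the COPM and the other clinical outcomes do not use the log. Neither the effect estimates nor the sample size changes.

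**The case against.** The best defence is that the undercount may be slight. The Table 2 wording can be read to include a walk or bus trip that starts as a home visit. Many Table 1 examples, such as dressing, preparing food, vacuuming and knitting, are activities normally done at home. The protocol does not say where supervision takes place, so some may fall within logged visits. A recording manual, not shown, may settle this. All of this stands as a limit on size. It does not remove the point: the wording in Outcomes and in Health economic analysis refers to time in the home, and if outings and supervision are meant to count, the three places should say so.

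A reader might go further and infer that the trial has no other record of treatment received, that delivery of the weekly therapist hour cannot be checked, and that contamination cannot be measured. The document does not support these readings.

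- The log is presented as a cost outcome, not as a measure of dose or fidelity.
- Table 2 also records, at 3, 9 and 15 months, whether and how often home-based assistance is in place, with reablement, occupational therapist and physiotherapist as separate categories. Day-centre, outpatient and inpatient care are recorded at 3 and 9 months.
- Therapist minutes in the log give at least a lower bound on the weekly hour, and therapist minutes in the control arm, with the reablement category, would show overt crossover.

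One narrower limit remains. The Discussion concedes that "it will not be possible to avoid the same health-care personnel providing both the experimental and control interventions" and that group differences may shrink as a result. If shared staff bring a reablement style into ordinary control visits, a log by profession will not show it. The protocol already discloses that route and its direction, and the log neither causes nor prevents it.

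**Conclusion.** The point holds as a costing problem. As defined, the log can miss staff time that the protocol itself describes as part of reablement, and the resulting error would tend to understate reablement's incremental cost. The direction rests on two readings of the text: that some out-of-home training and supervision falls outside logged home visits, and that control care contains less of such time. Both are likely; neither is certain, since some controls may receive therapist rehabilitation.

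The size cannot be derived from the document. The illustrative 0 to 6.5 therapist hours per reablement participant depends wholly on the assumed 0% to 50% share and on about 13 weeks of treatment, and zero is within what the text allows. The conclusion does not extend to the clinical effect estimates, and it does not mean that delivery or contamination goes unmeasured.

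**What to change.** In the Outcomes section, the t5 usage row of Table 2 and the Health economic analysis section, use one definition: all staff minutes spent with or for the participant, in either arm, inside or outside the home, including participant-specific supervision of home-care staff. Cost all of that time. If outings and supervision during visits are already meant to be included, say so in the same three places.

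Optionally, report therapist minutes by arm descriptively, as a partial check on the weekly therapist hour and on overt crossover. Control-arm training minutes should not be read as contamination in themselves, because standard care may legitimately include therapist rehabilitation.

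The cost is slightly more recording on a form already completed daily and, probably, a less favourable cost for reablement. The change should be made before logging starts, since daily minutes not recorded at the time are unlikely to be recoverable.

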**Table 2 Tab2:** **Summary of measures to be collected**

Outcome	Data collection instrument and scale	Time points
**Primary outcome measures**		
Activity performance	Canadian Occupational Performance Measure. Scale 1–10, 1 is low performance	t1, t2, t3
Satisfaction with activity performance	Canadian Occupational Performance Measure. Scale 1–10, 1 is low satisfaction	t1, t2, t3
**Secondary outcome measures**		
Lower extremity function and mobility	Timed Up and Go, measured in seconds, the second of two trials will be used	t1, t2, t3
Grip strength	Jamar dynamometer, measured in kilograms, the mean of two trials will be used	t1, t2, t3
Health-related quality of life	COOP/Wonka. Scale 1–5, 1 is low health-related quality of life	t1, t2, t3
**Other measures**		
Age	Years	t1
Gender	Female/Male	t1
Marital status	Married/Cohabiting/Single/Widowed/Separated or divorced	t1
Level of education	Primary school/High school/1–3 years university/> 4 years university	t1
History of paid work	Yes/No	t1
Profession	Type of work	t1
Current work status	Retired/Disability benefit/Working	t1, t2, t3
Motivation for rehabilitation	Numeric scale 1–10, 1 is lowest	t1
Main disease	Type of dominant disease	t1, t2, t3
Comorbidity	Presence of additional diseases	t1, t2, t3
Prescribed medication	Type and usage	t1, t2, t3
Un-prescribed medication	Type and usage	t1, t2, t3
Research assistant identification of participant’s group assignment	Yes/No	t2, t3
Control of research assistant’s identification of group assignment of participant	Intervention group/Control group	t2, t3
**Health-care services and cost measures**		
Warranted community-based assistance in time of inclusion	*Type of assistance wanted*	t1
	Home-helper/Nurse/Auxiliary nurse/Occupational therapist/Physiotherapist/Nursing home placement long term/Nursing home placement short term/Assisted living/Meals on Wheels/Safety alarm/Rehabilitation	
Inpatient and outpatient treatment since last assessment	*Frequency and type of co-interventions*	t2, t3
	Hospital admissions/Admissions to other institutions/Day centre placement/Outpatient treatment	
Current home-based assistance offered	*Presence and frequency of home-based assistance*	t2, t3, t4
	Home-helper/Nurse/Auxiliary nurse/Occupational therapist/Physiotherapist/Meals on Wheels/Reablement/No assistance	
Current community institution-based service offered	*Type of institution-based service offered*	t4
	Nursing home placement long-term/Nursing home placement short-term/Day placement/Other institution placement/No institution placement	
Usage of home-based services	*Daily time registration in minutes of working time used during home-visits*	t5
	Home-helper/Nurse/Auxiliary nurse/Occupational therapist/Physiotherapist/Social educator/Assistant/Speech therapist/Student	

t1 = baseline assessment, t2 = 3 months after baseline assessment, t3 = 9 months after baseline assessment, t4 = 15 months after baseline assessment, t5 = daily assessment during 9 months after baseline assessment.

